Lastly, few studies have adopted an intersectional approach to understanding mental health disparities among SGM persons. The existing literature in this area has predominantly focused on white, cisgender samples, overlooking the unique stressors faced by individuals who experience multiple forces of marginalization [52]. Emerging research, however, has emphasized the ways in which intersecting forces of oppression and marginalization may shape mental health disparities among diverse SGM subpopulations in the US [53–55]. For instance, one longitudinal study conducted among cisgender Black, Latino, and multiracial sexual minority men found that the interaction between racial discrimination and internalized sexual orientation-related stigma contributed to greater levels of depression, anxiety, and alcohol use over the 12-month follow-up period [54]. There is also evidence that minority stress reflected in the experiences of individuals who vary in gender identity, gender expression, and sexual orientation may contribute to further mental health disparities among SGM subgroups. Indeed, several studies have suggested that individuals who identify as both sexual *and* gender minorities (e.g., gay transmasculine persons, bisexual gender non-conforming persons) have significantly worse mental health outcomes compared to those who identify only as sexual *or* gender minorities [56, 57].

In summary, there is a need for longitudinal investigations that characterize the complex and nuanced interrelationships between minority stressors, mental health conditions, and suicidal behaviors over time among heterogeneous rural SGM adults. This is necessary to create more targeted, acceptable, and impactful intervention content and strategies that mitigate stigma, promote mental health, and prevent suicidal behaviors. In response to these needs, the current study will enroll and follow a large and diverse group of SGM adults living in rural and small metropolitan areas in the US. The study has two specific aims: (1) determine whether classes of stigma, discrimination, and traumatic experiences vary across subgroups of rural SGM adults and whether these exposure classes are associated with an increased *prevalence* of depression, suicidal ideation, and suicide attempts; and (2) determine whether the classes identified in Aim 1 are associated with an increased *incidence* of depression, suicidal ideation, and suicide attempts among rural SGM adults.

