### Sample size

We based our sample size calculations on limited previous studies capturing the prevalence of depression, suicidal ideation, and suicide attempts [1, 4, 7, 33, 63–71] – as well as distal minority stressors [34, 72, 73] – among SGM persons. For Aim 1, using conservative estimates, we expect a sample size of *N* = 500 in each SGM subgroup to provide a minimum of 98% power (normal approximation with continuity correction) to detect a 15% absolute difference in depression prevalence (estimated prevalence ratio of 1.6) between exposed and unexposed persons. We also expect this sample size to provide at minimum 98% power for a 15% absolute difference in both suicidal ideation and attempts. For the LCA, estimates of minimum required sample sizes in growth mixture models with 10 exposure measures ranged from 300 to 1,100 (in a six-class model with low class separation and 20% missing data) based on Monte Carlo simulations [74]. With an estimated 13 indicators of distal minority stressors, our total sample of 2,500 should therefore be adequate for estimating growth mixture models.

All participants will be followed for 12 months with a projected overall retention rate of 80% resulting in *N* = 400 participants in each SGM subgroup available for endline analyses. We will use the same retention procedures successfully implemented in a recent online prospective pilot study with gay men and other men who have sex with men that demonstrated retention rates of 98% at four months [75]. Though retention is not expected to vary by SGM subgroup, our Aim 2 power calculations account for expected variations in terms of the prevalence and incidence of depression and suicide attempts. Drawing on one general population study of depression incidence over a 24-month period [76], we have used a conservative estimate of average annual incidence of one-eighth of the estimated prevalence. We have also extrapolated from existing cross-sectional studies [7, 34, 66, 72, 73, 77, 78] to estimate that between 25–30% of participants will have additional exposures to distal minority stressors over the follow-up period.

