### Data analysis

For Aim 1, we will use latent class analysis (LCA) to explore how clusters of stigma, discrimination, and traumatic experiences (i.e., distal minority stressors) may be differentially associated with mental health-related outcomes among SGM persons at baseline. LCA is a person-centered analytic approach that allows for the identification of underlying classes of participants based on their responses to observed indicator variables [92]. Using the indicators described above to capture distal minority stressors, we will perform class enumeration by testing models with an increasing number of classes. The best fitting model will be selected using fit indices such as the Akaike Information Criteria, Bayesian Information Criteria, Vuong-Lo-Mendell-Rubin Likelihood Ratio Test, and entropy, and further evaluated based on theoretical interpretability [93]. All initial analyses will be conducted separately by the five SGM subgroups (sexual minority cisgender women, sexual minority cisgender men, transgender women and transfeminine persons, transgender men and transmasculine persons, and non-binary persons). Various modeling approaches will be examined to address potential effect modification by sexual orientation or gender identity within these five subgroups, and multigroup alignment optimization will be used to assess measurement invariance. If the latent classes are similar across subgroups, we will combine and repeat the effect modification and optimization analysis for gender minority versus cisgender participants. Finally, we will use the Bolck, Croon, and Hagenaars latent class regression approach to assess associations between class membership and prevalent depression, suicidal ideation, and suicide attempts [94]. In addition, age and racial/ethnic identities will be included as covariates, with possible interactions with latent class.

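### The only invariance method named, alignment optimization, is a factor-model method and does not test whether the planned latent classes are the same across the five subgroups

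*Protocol article*

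**What the plan says.** The Background section sets the first part of Aim 1 as a question about differences between subgroups: "determine whether classes of stigma, discrimination, and traumatic experiences vary across subgroups of rural SGM adults". The second part asks whether the classes are associated with prevalent depression, suicidal ideation and suicide attempts.

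The Data analysis section of the Protocol article gives the method:

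- The measurement model is a latent class model: "we will use latent class analysis (LCA) to explore how clusters of stigma, discrimination, and traumatic experiences".
- The number of classes is chosen from several fit indices (AIC, BIC, a likelihood-ratio test, entropy) and from interpretability.
- The first fits are separate: "All initial analyses will be conducted separately by the five SGM subgroups".
- Two tools follow in one sentence. The first is open-ended: "Various modeling approaches will be examined to address potential effect modification by sexual orientation or gender identity within these five subgroups". The second is specific: "multigroup alignment optimization will be used to assess measurement invariance".
- A decision follows: "If the latent classes are similar across subgroups, we will combine and repeat the effect modification and optimization analysis", this time contrasting gender minority with cisgender participants.

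The Sample size section supplies two figures that matter for the size of any formal comparison: "With an estimated 13 indicators of distal minority stressors" and "we expect a sample size of *N* = 500 in each SGM subgroup".

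**The concern.** The invariance method and the measurement model belong to different families. Alignment was built for factor models. It chooses each group's factor mean and variance so that loadings and intercepts or thresholds differ as little as possible between groups. A latent class model has neither a factor mean nor a loading. Its measurement parameters are the probabilities of endorsing each indicator within each class, and its structural parameters are the class sizes.

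Two things depend on the comparison. It answers the first question of Aim 1. It also decides whether subgroups are combined for the gender-minority versus cisgender analysis. The article states no criterion for calling classes similar, so the alignment step is the only named method that could inform the decision. If it does not act on the class parameters, the decision has no stated formal basis.

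**Working it through.** The article states no figure for this step, so there is none to reproduce. The check has three parts.

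**1. What alignment needs, and whether an LCA has it.**

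Inputs: 13 indicators (Sample size section, an estimate), taken as binary (assumption).

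One-factor model in a single group: logit P(item j = 1) = b_j + a_j(m + s·x), with x standard normal. Setting a_j′ = a_j·s, b_j′ = b_j + a_j·m, m′ = 0 and s′ = 1 leaves every response probability unchanged. So m and s are not determined by the data of that group alone. They are the two quantities that alignment chooses.

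- Parameters: 13 loadings + 13 intercepts + mean + variance = 28.
- Numerical rank of the Jacobian of the 2^13 response-pattern probabilities: 26.
- Undetermined: 28 − 26 = 2, as the algebra says.

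LCA with K classes: (K − 1) class sizes + 13K item-response probabilities.

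| K | Parameters | Rank | Undetermined |
|---|---|---|---|
| 2 | 1 + 26 = 27 | 27 | 0 |
| 3 | 2 + 39 = 41 | 41 | 0 |
| 4 | 3 + 52 = 55 | 55 | 0 |

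Apart from the labelling of classes, the LCA leaves no free latent scale in each group, so standard alignment has nothing to optimise. The rank check used simulated item parameters and covers K = 2 to 4. It shows local identification only.

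**2. Where the text places alignment.**

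The sentence that names it does not say which parameters or model it applies to. The next sentence makes the combining of subgroups depend on the similarity of the latent classes and then repeats the optimization step. That wording ties alignment to the classes. The Aim 1 analysis mentions no factor model.

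**3. Size of the conventional comparison.**

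The article does not fix K, so a range of 2 to 6 is shown. With five groups, the free model has 5(13K + K − 1) parameters. The model with equal item-response probabilities has 13K + 5(K − 1). The difference is 4 × 13K = 52K.

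| K | Equal item probabilities, 5 groups (52K) | Equal class sizes, 5 groups, 4(K − 1) | Equal item probabilities, gender minority v cisgender (13K) |
|---|---|---|---|
| 2 | 104 | 4 | 26 |
| 3 | 156 | 8 | 39 |
| 4 | 208 | 12 | 52 |
| 5 | 260 | 16 | 65 |
| 6 | 312 | 20 | 78 |

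With 500 persons per subgroup, the chi-square reference for a single test on 104 to 312 degrees of freedom may be unreliable. This affects how the replacement should be worded.

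**The case against.** The strongest reply is that the article does not say what alignment is applied to. The stigma and discrimination exposures come from multi-item scales that could be factor-modelled, and structural equation mixture models are planned for Aim 2. Alignment of such a factor across subgroups would be legitimate. This reading is possible, but it is not stated and sits badly with the sentence that follows. It would also still not show whether the classes vary.

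A second reply is that this is a condensed article, and that nested model sequences and pooling criteria are commonly left to a fuller document. That is fair for detail. The point here is different: the one invariance method that the article does name does not, in standard form, fit the model it stands beside.

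Three stronger readings go further than the text allows:

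- **A reader might infer that the plan has no valid way to compare classes.** Separate enumeration permits a sound descriptive comparison of class number and profile. The open wording on modelling approaches, although directed at effect modification within subgroups, does not exclude a multiple-group LCA.
- **A reader might infer that pooled incidence analyses depend on this step.** The text makes only the gender-minority versus cisgender repeat conditional. Aim 2 begins with analyses stratified by subgroup, and the class-outcome regressions of Aim 1 can run within each subgroup without invariance across subgroups.
- **A reader might infer that comparing separate solutions would usually show false differences.** Simulations with identical truth in all five groups, n = 500 and selection by BIC alone do not support this in general. The chance that all five agree on the number of classes ran from about 0.1 to 1.0. Low values arose with six weakly separated classes. The article fixes neither the number of classes nor their separation, and it does not select by BIC alone.

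**Conclusion.** The concern holds in a limited form. The only method named for measurement invariance is, in standard form, a factor-model method. It does not test whether class-specific item-response probabilities or class sizes are equal across the five subgroups. The article names no formal comparison of classes, although this is the first question of Aim 1 and governs whether subgroups are combined for one later analysis.

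The effect is confined to that question and that decision. No sample size, power figure or within-subgroup association is affected. The conclusion assumes that alignment is used in its standard form and is directed at the classes, as its placement suggests. If it was meant for a separate factor model, the method is sound for that purpose, but a named class comparison is still lacking. This is a change that should be made, at low cost.

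**What to change.** Replace the alignment sentence with a multiple-group LCA, with SGM subgroup as the known group and a common number of classes. The separate fits stay as the first step and inform that number. Then compare in sequence:

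1. item-response probabilities free in each subgroup;
2. item-response probabilities equal across subgroups (measurement invariance);
3. class sizes equal as well.

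If the second model is rejected, free only the indicators that differ (partial invariance). State that subgroups are combined when full or partial invariance holds.

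Base the decision on BIC or a bootstrap likelihood-ratio test, not on the global chi-square alone.

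If alignment is intended for a factor model of the stigma or discrimination scales, say so, and still name the multiple-group LCA for the classes.

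The cost is about one paragraph of text and modest extra analysis work. It needs standard LCA software and no new data.

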## Discussion

REALM, as a prospective cohort study focused on both sexual minority and gender minority adults living in rural areas of the US, presents a critical opportunity to better understand how minority stress contributes to adverse mental health outcomes and suicidal behaviors among populations that remain underrepresented in research and programs in 2024. By recruiting a large and heterogeneous sample of rural SGM adults that can be followed prospectively, REALM aims not only to identify patterns of exposure to distal minority stressors (e.g., stigma, discrimination, and traumatic experiences) that influence both the prevalence and incidence of depression, suicidal ideation, and suicide attempts through multiple complex pathways, but also to integrate factors from suicide-focused theories, consider key protective factors, and explore diversity within SGM communities. Given the lack of established mechanisms for reaching rural SGM populations, this study will leverage online methods to recruit and retain up to 2,500 persons.

REALM is poised to fill a sizeable gap in evidence around mental health among SGM adults living in rural areas, with implications for the development of responsive interventions. It is important to highlight that for gender minority populations, specifically, prevalence data on mental health conditions and suicidal behaviors are lacking even in urban settings. While newer initiatives like the 2015 and 2022 US Transgender Surveys [25] and the Leading Innovation for Transgender Women’s Health and Empowerment (LITE) Cohort Study [98] are beginning to fill these gaps, they are either cross-sectional, urban, or predominantly focused on sexual health. As such, REALM will provide complementary rather than overlapping information to these important initiatives.

There are several potential drivers of this limited focus on mental health among rural SGM adults. Most importantly, these populations may be harder to identify and reach given rural–urban differences related to identity disclosure, socialization and congregation, and the availability of SGM-specific health services and other resources [40, 99–101]. Our study seeks to address this challenge by drawing upon established methods of online recruitment for SGM populations that can be geotargeted, with the potential to combine these efforts with advertising and recruitment in physical spaces guided by input from our CAB. Secondly, collecting information on suicidal ideation and behaviors has ethical implications given the need to ensure participants’ safety, and represents a greater investment from both researchers and participants in the study. For SGM populations, this can be particularly fraught as there are concerns about unintentionally outing someone when talking to an emergency contact, whether services will be safe or affirming, and the potential for structural stigma to be enacted through different institutions that would be called upon to help ensure safety (e.g., police force, healthcare providers). The REALM CAB, representation of lived experience among the research team, interdisciplinary collaboration, and careful and intensive planning were critical to ensuring that rigorous safety procedures, that take these concerns into consideration, could be established. These resources can help guide future studies that face similar challenges.

There are several possible limitations to REALM that must be acknowledged. First, there is potential for this study to fall short of the targeted enrollment sizes by stratified subgroup. We will adjust recruitment strategies based on real-time monitoring of recruitment outcomes to ensure representation across cohorts of SGM adults with different identities and by race/ethnicity. Second, online procedures may pose challenges to retention [102], although we have shown high retention in prior virtual cohort studies that have employed similar retention procedures and therefore do not anticipate this issue [103–105]. Third, previous research has shown that online study procedures can result in biases in both enrollment and retention compared to the general population [102, 106]. However, the online study processes we have developed over the past several years have resulted in study samples that are approximately consistent with general US population estimates in terms of race/ethnicity and urbanicity [107–109]. Lastly, engagement in study procedures may systematically vary by the primary exposures and outcomes of interest. We will examine the potential for these biases as the study is being conducted and employ statistical approaches to address systematic biases in missing data if necessary [110, 111].

Understanding the processes through which minority stressors shape the mental health of diverse SGM persons living in rural areas of the US is critical to building outreach approaches and preventive interventions that can engage understudied groups of SGM adults who experience health disparities and limited access to affirming and effective resources. As policy landscapes change throughout the US, and structural stigma and violence continue to shape the lived realities of SGM communities, efforts to protect and promote mental health are both timely and essential. By being grounded in minority stress and suicide theories, using established online and diversified recruitment methods to reach underprioritized populations, ensuring enrollment of SGM adults with diverse identities, cultivating and nurturing a diverse study team, and collaborating closely with a CAB with relevant lived experience, REALM will work to address key gaps in knowledge on the processes that produce poor mental health among rural SGM adults in the US. In doing so, REALM will generate strategies for how best to support well-being among these vulnerable populations. Most immediately, this will include leveraging REALM’s online sample to inform the development of a novel technology-delivered depression support and suicide prevention intervention, with participatory processes used to help ensure that content and delivery strategies are tailored, acceptable, and relevant to the target population. The cohort data set, by being made accessible in a National Institute of Mental Health online repository, will also be available to support other secondary analyses that can further inform interventions to promote mental health and well-being for SGM adults in rural areas.

## Data Availability

The data associated with this study will be uploaded to the National Institute of Mental Health Data Archive for public use [128].

## Abbreviations

SGM: Sexual and gender minority
LGBTQ: Lesbian, gay, bisexual, transgender, and queer
US: United States
IPTS: Interpersonal-Psychological Theory of Suicidal Behavior
REALM: Rural Exploration and Approaches for LGBTQ + Mental Health
CAB: Community Advisory Board
PHQ-9: Patient Health Questionnaire-9
C-SSRS: Columbia Suicide Severity Rating Scale
LCA: Latent class analysis
